## Method

### Participants

This study is a randomized, single-blind, parallel-group controlled trial of 6 months duration. Follow-up reviews will be conducted in 3, 5, and 7 days, and 1, 3, and 6 months after enrollment. Multiple calls will be made 1 week before each follow-up visit to remind participants of their visit. The study was approved by the Biomedical Ethics Committee of Anhui Medical University (reference number: 20170095, see additional file 1) and registered at the ClinicalTrials.gov provided by the US National Library of Medicine (Registration No.: NCT04095780). The protocol was written according to the SPIRIT Checklist (Standard Protocol Items: Recommendations for Interventional Trials, see additional file 2).

The study is being conducted at The Second People’s Hospital of Hefei, Hefei Hospital Affiliated to Anhui Medical University, Hefei, China. This hospital is one of the largest general hospitals in Hefei, which is the capital city of Anhui province. Patients with stroke in acute phase receive care at the Inpatient Stroke Unit, Department of Neurology, and will form the study subjects for this trial. During their inpatient stay in the Stroke Unit, they receive multidisciplinary treatments and support involving physiotherapy, occupational and speech therapy, and social work service. The length of hospitalization is usually 1 week. After discharge, patients with stroke are scheduled for regular follow-ups and outpatient rehabilitation. Our oral health research team is collaborating with the Stroke Unit in helping with oral care for those patients following stroke.

The following selection criteria are applied: (1) having onset of stroke within 3 days and free of any post-stroke complication; (2) having moderate to severe functional disability—Barthel Index (BI) scores of < 70; (3) being conscious and respiring voluntarily without ventilator; (4) not having any lung disease and lower respiratory infection; (5) not having indwelling naso-gastric feeding tubes; (6) having dysphagia as shown by Gugging Swallowing Screen (GUSS) test; (7) having normal cognitive ability or mild impairment—Mini-Mental State Examination (MMSE) > 18; (7) having the ability to follow instructions (as an assessment of compliance of oral health intervention); (8) not having systemic administration of antibiotics; and (9) not being edentulous. Patients who meet the above selection criteria will be provided with detailed information regarding potential benefits and adverse effects of the interventions, the procedures of this trial, and the anticipated outcomes. They will be asked by a researcher in our team to sign on a written informed consent before enrolling in this study (written informed consent, additional file 3).

According previous studies [12, 13], pneumonia complicating stroke usually occurs within 1 week after stroke. We set the prevalence of pneumonia within 1 week after onset of stroke as the primary outcome of this study since we would like to explore whether oral health promotion interventions could possibly reduce the prevalence of pneumonia after stroke. According to previous epidemiological studies, the prevalence of pneumonia complicating stroke is 20 to 60% [12, 13]. Thus, we hypothesize that in the comparison group, the prevalence of pneumonia complicating stroke within 1 week is 40%, while the prevalence could be decreased to the lower limit of 20% in the interventional group. We set the statistical power at 80% and the statistical significance level at 0.05. Anticipating a 10% dropout rate over the first week of this clinical trial, the initial sample size for each group is proposed as 83 patients per group (166 subjects in total, Gpower 3.0.10 statistical software).

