#### Data management

The principal investigator will oversee the data collection, entry, analyses, and reporting. Two researchers in our team will conduct data proofreading after the completion of data entry. The data will be securely stored in SPSS files in a computer with a password. The statistics software packages SPSS 25 for Windows (SPSS Inc., Chicago, USA) and QIIME 2 will be used to analyze the data. Per-protocol (PP) will be employed for both primary and secondary outcomes in bivariate analyses. Within- and between-group comparisons will be conducted over the clinical trial period. When the outcome variables are continuous and follow a normal distribution, a paired *t* test for related samples will be performed to determine the significant differences over time within a group. The Student *t* test for independent samples will be performed to compare the mean of the outcomes between the groups at baseline and follow-up reviews. When the outcome variables are continuous but do not follow a normal distribution, the Wilcoxon signed-rank test will be performed to determine the significant differences over time within a group. The Mann-Whitney *U* test will be employed to compare the differences in the rank of outcomes between the groups at baseline and follow-up reviews. When the outcome variables are categorical, the McNemar test will be performed to identify the changes in prevalence over time within a group. The chi-square test will be employed to compare the variations in prevalence between the groups at baseline and follow-up reviews. Regression analyses will be employed to address the effect of confounding factors for outcomes. When conducting the regression analysis, the method of Last Observation Carried Forward (LOCF) will be employed to deal with missing outcomes at follow-up reviews. Linear regression will be adopted when the dependent variables are continuous, and the residuals of the regression followed a normal distribution. Negative binomial regression will be adopted when the distribution of the continuous dependent variables is over-dispersed. Logistic regression will be adopted when the dependent variables are binary.

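### 83 per group, 10% dropout and 80% power cannot all hold for a two-sided 0.05 chi-square test of 40% versus 20%; about 75 evaluable per group gives about 77% power

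*Protocol article*

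**What the plan says.** The sample-size paragraph is in the Participants section of the protocol article. Its inputs are:

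- Comparison group: "in the comparison group, the prevalence of pneumonia complicating stroke within 1 week is 40" per cent.
- Intervention group: "the prevalence could be decreased to the lower limit of 20% in the interventional group".
- Error rates: "We set the statistical power at 80% and the statistical significance level at 0.05". Sidedness is not given.
- Dropout and result: "Anticipating a 10% dropout rate over the first week of this clinical trial, the initial sample size for each group is proposed as 83".
- Total and software: "83 patients per group (166 subjects in total, Gpower 3.0.10 statistical software".

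The paragraph gives no number before dropout and does not say which test was selected in the software. Under Data management the between-group test for categorical outcomes is fixed: "The chi-square test will be employed to compare the variations in prevalence between the groups at baseline and follow-up reviews". The same section analyses primary and secondary outcomes per protocol in the bivariate comparisons.

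**The concern.** The paragraph presents 83 as a number that already allows for 10% loss in the first week. Yet 83 is almost exactly what a two-sided chi-square test of 40% versus 20% needs with no loss at all. If patients drop out as expected, the primary comparison is then made on fewer patients than the 80% power requires. The loss does reach that comparison, because the chi-square test is run on the per-protocol set. A reader of a null result would credit the trial with more power than it has for the stated effect.

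**Working it through.** **Inputs.** p1 = 0.40, p2 = 0.20, difference 0.20, power 80%, level 0.05, dropout 10%, all from Participants. Allocation is 1:1 (Background). The chi-square test is from Data management. Two-sided testing is an assumption: it is the usual convention and fits the non-directional chi-square test, but the article does not state it.

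**Reproducing 83 without dropout (two-sided 0.05).**

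- Chi-square effect size: the cells differ from expectation by 0.05, so w² = 2 × 0.0025/0.15 + 2 × 0.0025/0.35 = 0.0476 and w = 0.218. This needs N = 165, which is 83 per group, or 166 in total. These are the plan's figures.
- Pooled z formula: n = [1.960 × √(2 × 0.30 × 0.70) + 0.842 × √(0.40 × 0.60 + 0.20 × 0.80)]² / 0.20² = (1.2702 + 0.5323)² / 0.04 = 81.2, so 82 per group.

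**Adding the dropout.** 82/0.9 = 91.1, so 92 per group; 83/0.9 = 92.2, so 93 per group.

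**Search for a method that gives 83 with dropout included.**

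| Method | Evaluable per group | After /0.9 |
|---|---|---|
| Two-sided, pooled z | 82 | 92 |
| Two-sided, unpooled | 79 | 88 |
| Two-sided, arcsine | 81 | 90 |
| Two-sided, continuity-corrected | 91 | 102 |
| Two-sided Fisher exact | 90 | 100 |
| One-sided, pooled z | 64 | 72 |
| One-sided, continuity-corrected | 74 | 83 |
| One-sided Fisher exact | 73 | 82 |

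No two-sided method tried gives 83 after dropout. The one-sided continuity-corrected formula does: the uncorrected n is 63.9, and the correction n/4 × [1 + √(1 + 4/(n × 0.20))]² gives 73.5, so 74; then 74/0.9 = 82.2, so 83. One-sided Fisher first reaches 80% at 73 per group (80.3%), which rounds up to 82 after dropout. It also has 80.3% power at 74, which would give 83.

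**Power with the stated dropout.** 83 × 0.9 = 74.7 evaluable per group.

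- Two-sided pooled z: (0.20 × √74.7 − 1.2702)/0.6325 = 0.725, so 76.6%. At 74 it is 76.2% and at 75 it is 76.7%.
- Exact enumeration of the two-sided chi-square: 76.9% at 74 and 76.8% at 75.
- Two-sided Fisher: 70.5% at 74 and 71.4% at 75.
- With all 83 evaluable, two-sided pooled z: 80.9%.
- One-sided 0.05 at 74 to 75: 85.0% to 85.4% by pooled z, 80.3% to 80.9% by Fisher.

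**The case against.** The strongest objection is that the article never says the test is two-sided. It says that dropout was anticipated and words the hypothesis as a decrease. A one-sided 0.05 calculation with continuity correction gives exactly 83 with the dropout included, so a reader who infers that the allowance was certainly forgotten goes beyond the document. This stands: the cause is not established. It would also be too strong to say that no test gives the design 80% power, since a one-sided test at 74 to 75 per group reaches it.

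This does not make the paragraph consistent. The one-sided route needs a level that is not disclosed and a sizing method that differs from the chi-square test named in the same article. The plain one-sided formula, without correction, gives 72 after dropout, not 83.

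A second objection is that a condensed article may leave sidedness and test family to a fuller document. That is fair as to the omission. But the point is not that details are absent: the inputs and the result that are printed do not agree under the test that is printed.

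A third objection is size. The gap is about 3 percentage points, and at 74.7 per group an intervention rate of 19.2% instead of 20% would restore 80%. The 40% is itself taken from a cited range of 20% to 60%, a much larger uncertainty. This also stands, and it limits the remedy to a corrected statement.

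**Conclusion.** The paragraph is wrong as written for the planned test. At two-sided 0.05, a chi-square comparison of 40% versus 20% needs 82 to 83 evaluable per group. With 83 randomised and 10% lost, about 75 remain and power is about 77%. This rests on the article's own rates and dropout and on reading the chi-square test as two-sided. Either the dropout allowance was omitted, or an undisclosed one-sided calculation was used that does not match the analysis; the article does not let a reader decide which.

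A reader might also infer that the per-protocol set pushes power well below 77%. Non-adherence could remove further patients from the chi-square comparison, but the article gives no rate, so no figure can be put on it. Per protocol is specified for the bivariate analyses; the regressions carry the last observation forward. Nor does the finding show that more patients must be recruited.

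**What to change.** Keep 166 randomised and restate the end of the sample-size paragraph along these lines:

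> 166 patients will be randomised (83 per group). After 10% dropout about 75 per group will be evaluable, giving about 77% power to detect 40% versus 20% with a chi-square test at two-sided 0.05. Without dropout, 80% power requires 83 per group (total N = 165 by the chi-square effect-size method).

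The sentence should carry the test, the sidedness and the number before dropout. If a one-sided test was intended, state that, with the continuity correction and the 74 evaluable per group, and change Data management so that the primary comparison is the test that was sized.

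The cost is one corrected sentence and a slightly less favourable stated power. Should the sponsor prefer to keep 80% after dropout with a two-sided chi-square test, the arithmetic gives 92 to 93 per group (184 to 186 in total), that is 18 to 20 more patients.

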### Interventions

Participants will be block randomized to one to the two groups with a block size of 4: (1) comparison group—oral hygiene instruction (OHI)—or (2) interventional group—powered tooth brushing, 0.2% chlorhexidine gluconate mouth rinse (10 ml twice daily), and OHI. This clinical trial is single blinded with researchers blinded to the allocations while subjects are aware of it. A researcher in our oral health research team who is not involved in recruiting participants or assessing outcomes will use SPSS 25 for Windows (SPSS Inc., Chicago, USA) to generate the randomized sequence. Another researcher in our team who is responsible for participant screening/recruitment and outcome assessment will be blinded to the treatment assignment until the end of this trial. The allocation sequence number will be concealed in an opaque envelope and provided to a staff at the stroke unit who is independent of our team. The staff is responsible for assigning subjects to one of the two groups after enrollment. After the end of this study, the staff will reveal the allocation sequence. Participants in the interventional group will be asked to bring back their powered toothbrush and empty bottles of chlorhexidine mouthwash for replacement at follow-up visits after discharge. This strategy may improve adherence to intervention protocols.

Immediately after group assignment, the subjects and their primary caregivers in the interventional group will be invited to a one-to-one workshop provided by a dental professional regarding oral hygiene. This content of this workshop includes the importance of oral health following stroke and how to implement standardized oral hygiene care (Bass brushing technique, flossing, mouthwash use, and cleaning partial dentures). The primary caregivers will be responsible for carrying out the oral hygiene care for the patients with stroke. After the demonstration, the primary caregivers will be asked to perform their oral hygiene care skills and will be corrected by the dental professional if oral health care is not conducted appropriately. For those in the interventional group, they will be provided with a powered toothbrush and its manufacturer instructions. In addition, they will be given 0.2% chlorhexidine gluconate mouthwash. They will be asked to use a powered toothbrush to brush their teeth and rinse twice daily with 10 ml of the mouth rinse (at least 30 min after brushing). For those subjects in the comparison group, they will be only provided with oral hygiene instruction in the one-to-one workshop. Due to ethical considerations, those subjects in the comparison group will be given the same oral hygiene products after the completion of the clinical trial. Participants may withdraw from this study at any time points. Participants who will have systemic antibiotic use longer than 1 week after interventions will be excluded from this study.

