Next-generation sequencing (NGS) technique at the 16S rRNA level will be employed in this proposed trial to assess the change of the composition and relative abundance in the oral microbial community. NGS technique enables us to sequence a great number of genes at one time and profile taxonomic composition at the genus or species level with a deeper coverage of microbial community [20].

We proposed this randomized controlled, parallel, single-blinded, equivalence trial with an allocation ratio of 1:1, which compares the effectiveness of powered tooth brushing with adjunctive use of chlorhexidine mouth rinsing and oral health instruction (OHI) versus OHI in (1) reducing the prevalence of aspiration pneumonia complicating stroke, (2) changing the composition and relative abundance in the oral microbial community, (3) improving oral hygiene status in terms of reducing dental plaque and gingival bleeding, and (4) improving oral health-/generic health-related quality of life.

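### Assessor blinding is not protected at the post-discharge visits, to which only intervention patients are asked to bring their toothbrush and chlorhexidine bottles

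*Protocol article*

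**What the plan says.** All of the following is in the protocol article, under Interventions unless another section is named.

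- **Blinding:** "This clinical trial is single blinded with researchers blinded to the allocations while subjects are aware of it". One researcher combines two roles: the person "responsible for participant screening/recruitment and outcome assessment will be blinded to the treatment assignment until the end of this trial".
- **Product returns:** "Participants in the interventional group will be asked to bring back their powered toothbrush and empty bottles of chlorhexidine mouthwash for replacement at follow-up visits". The sentence goes on to limit this to visits after discharge, and the next one gives better adherence as the purpose. Comparison patients are given the products only once the trial is complete.
- **Allocation:** patients are "block randomized to one to the two groups with a block size of 4". The sequence is generated by a different researcher, "who is not involved in recruiting participants or assessing outcomes will use SPSS 25 for Windows". It is "concealed in an opaque envelope and provided to a staff at the stroke unit who is independent of our team". That person allocates each patient, and does so only once the patient has been enrolled.
- **Visits and outcomes:** reviews fall on days 3, 5 and 7 and at months 1, 3 and 6, and the hospital stay is usually 1 week (Participants). Plaque, gingival bleeding and quality of life are measured at months 1, 3 and 6. Pneumonia within 1 week is the primary outcome, and pneumonia by months 1, 3 and 6 is secondary (Outcomes). After discharge, pneumonia is diagnosed from the patient's history and medical notes (Assessment of pneumonia complicating stroke).

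**The concern.** Two instructions in one section work against each other. One requires the assessor to remain unaware of the arm to the end. The other has one arm alone arrive at the assessment visits with objects that disclose it. The article does not say who receives the products, when in the visit this happens, or that participants should keep their group to themselves.

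At stake is whether the 1-, 3- and 6-month clinical findings can be reported as blinded. The plaque outcome is the percentage of sites scored 2 or 3, so it turns on the examiner's line between plaque found only with a probe and a moderate amount. Bleeding is provoked by the examiner's own probing. Post-discharge pneumonia depends partly on how the history is taken. The planned re-scoring of about 10% of subjects measures intra-rater reliability, so it would not reveal an examiner who scores the two arms consistently but differently.

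A smaller concern follows from the dual role. If the assessor learns the arms of recent patients while still recruiting, a known fixed block of 4 makes some later assignments foreseeable.

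**Working it through.** The plan gives no figure of its own on this point. The blinding part is settled by comparing passages. The block-size part can be calculated.

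**1. Which outcomes the returns reach**

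| Outcome | When | Exposed to the returns? |
|---|---|---|
| Pneumonia within 1 week (primary) | Mostly in hospital | Largely no: returns start after discharge |
| Plaque, gingival bleeding | Months 1, 3, 6 | Yes: examiner-scored at the same visits |
| Later pneumonia | By months 1, 3, 6 | In part: history is taken at the visit, but medical notes and published criteria are also used |
| SF-12, OHIP-14, GOHAI | Months 1, 3, 6 | Little added: fixed-response answers from patients who know their arm |
| Oral rinse sequencing | Days 3, 5, 7; months 1, 3, 6 | Little: a laboratory read-out |

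**2. Predictability with blocks of 4**

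Inputs: block size 4 (Interventions) and a 1:1 ratio (Background). The assumption is that the recruiter knows every earlier assignment in the current block. There are six equally likely blocks: AABB, ABAB, ABBA, BAAB, BABA, BBAA.

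- Certain assignments: two in each of AABB and BBAA (third and fourth places), one in each of the other four (fourth place). Mean = (2×2 + 4×1)/6 = 8/6 = 1.333 of 4, or **33.3%**, about 55 of 166 patients.
- Correct guesses when always naming the arm with more places left: first place 1/2; second place 4/6; third place 2/6×1 + 4/6×1/2 = 4/6; fourth place 1. Sum = 0.500 + 0.667 + 0.667 + 1.000 = 2.833 of 4, or **70.8%**, against 50% with nothing known.
- The same enumeration gives 25.0% certain and 68.3% guessed for a fixed block of 6, and 20.0% and 66.6% for a fixed block of 8.

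**3. Could the returns supply that knowledge in time?**

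The accrual rate is not stated, so evenly spaced enrolment is assumed. Let L be the time from a patient's enrolment to the visit that reveals the arm. The first patient's arm can inform the fourth place only if three enrolment gaps exceed L, which means fewer than 3 patients per L. Knowing every earlier assignment needs each gap to exceed L, which means fewer than 1 patient per L.

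| Revealing visit | Any information | All earlier assignments known |
|---|---|---|
| Month 1 | Below about 3 per month: 166/3, over 55 months of accrual | Below about 1 per month: 166 months |
| Day 7 | Below about 3 per week: 166/3 ≈ 55 weeks, about 13 months | Below 1 per week: 166 weeks, about 38 months |
| Day 3 | Below about 1 per day: 166 days | Below 1 per 3 days: 166×3 = 498 days, about 16 months |

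Returns at month 1 would therefore rarely inform an open block. The day-3 and day-7 rows matter only if the arm leaks on the ward, or at a day-7 review after an early discharge.

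**The case against.** A reader might infer that blinding and allocation concealment do not hold. The documents do not support that.

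- **Exposure is not stated.** The text does not say that the assessor receives or sees the returns. The independent staff member, or the dental professional who runs the workshop, could handle them, and a journal article may leave such logistics to the full protocol. This stands: the right word is unprotected. It does not dispose of the point, because the article itself fixes a cue carried by one arm to visits where a blinded assessment is promised.
- **Concealment is sound in form.** It has a separate generator, an opaque envelope, independent staff and assignment after enrolment. This stands too. A fixed block of 4 is no breach in itself and matters only after a leak.
- **The 33% and 71% are worst-case figures.** They assume that all earlier assignments in the block are known, and nothing in the article says how likely that is. They should not be read as expected values. Eligibility also rests largely on defined thresholds, which limits how far recruitment could be steered.
- **The reach is limited.** The returns largely miss the primary outcome, and masking the assessor cannot mask the patients who report quality of life. Both stand.

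There is a ward route to a leak: products are given soon after assignment, patients know their arm, and reviews take place on days 3, 5 and 7. It is an inference from the design, and the article describes no such disclosure.

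**Conclusion.** The point holds in a limited form. As described, the product returns work against the promise of a blinded assessor, and nothing stated protects that promise at the 1-, 3- and 6-month visits. The exposed outcomes are plaque, gingival bleeding and, in part, post-discharge pneumonia. All are secondary. The primary outcome is largely unaffected by the returns, and the quality-of-life results are open to the participant's knowledge of the arm by design. The size of any bias cannot be derived from the article.

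The fixed block of 4 is a secondary matter. It would amplify a leak, up to 33.3% of assignments certain and 70.8% guessed correctly, on the assumption that every earlier assignment in the block is known. Month-1 returns would rarely provide that, so the main protection is to keep the recruiter-assessor unaware of assignments.

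**What to change.** 1. State that the independent stroke-unit staff member who already holds the allocation collects and replaces the products before the assessment and out of the assessor's sight.
2. Tell participants and caregivers not to mention their products or group to the assessor, on the ward as well as at later visits.
3. As an extra safeguard, generate the sequence for patients not yet randomised with randomly varying block sizes (for example 4 and 6) that are not disclosed to the recruiter-assessor.

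The first two steps cost a small change in visit order and some of the existing staff member's time. The third costs a regenerated list and a slightly larger possible imbalance when recruitment stops. Its gain is modest and was not calculated for varying sizes; a larger fixed block alone would help little (a fixed 6 still gives 68.3% guessed correctly). Sample size, treatments and outcomes do not change. If the full protocol already separates the exchange from the assessment, a sentence saying so is enough for the first step.

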### Outcomes

The primary outcome is the prevalence of pneumonia complicating stroke within 1 week after baseline. The secondary outcomes include the following: (1) the prevalence of pneumonia complicating stroke within 1, 3, and 6 months after baseline; (2) metagenomic outcomes in terms of composition and relative abundance of oral microbiome in oral rinse samples in 3, 5, and 7 days, and 1, 3, and 6 months after baseline; (3) oral hygiene status and gingival bleeding in 1, 3, and 6 months after baseline; and (4) generic health-/oral health-related quality of life in 1, 3, and 6 months after baseline. The time point for assessing each outcome is illustrated in Fig. 1.

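### The exclusion after randomisation for more than 1 week of antibiotics, combined with a per-protocol analysis, can drop some pneumonia cases from the pneumonia outcomes

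*Protocol article*

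**What the plan says.** - **Interventions:** "Participants who will have systemic antibiotic use longer than 1 week after interventions will be excluded from this study". Nothing is said about why the antibiotics were given. Group assignment comes first, so this is an exclusion after randomisation.
- **Outcomes:** "The primary outcome is the prevalence of pneumonia complicating stroke within 1 week after baseline". The first secondary outcome is "the prevalence of pneumonia complicating stroke within 1, 3, and 6 months after baseline".
- **Participants:** entry requires "not having systemic administration of antibiotics", no lower respiratory infection and no post-stroke complication. Any course that triggers the exclusion therefore begins during the trial. The sample size assumes pneumonia within 1 week in 40% of the comparison group, and that "the prevalence could be decreased to the lower limit of 20% in the interventional group".
- **Data management:** "Per-protocol (PP) will be employed for both primary and secondary outcomes in bivariate analyses". No intention-to-treat analysis is named. For the regression analyses, "the method of Last Observation Carried Forward (LOCF) will be employed to deal with missing outcomes at follow-up reviews".

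The article does not say whether a pneumonia recorded before exclusion stays in the analysis.

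**The concern.** Pneumonia is a plausible reason for a systemic antibiotic course in this population. A rule that excludes randomised participants for such a course is therefore tied to the outcome, and the per-protocol analysis offers no protection against it.

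The sentence can be read in two ways:

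- **A course lasting longer than 1 week.** Pneumonia cases treated for that long can leave the primary and the later pneumonia outcomes.
- **Use later than 1 week after the intervention starts.** Cases can leave the 1-, 3- and 6-month outcomes.

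An excluded case leaves both the numerator and the denominator of its arm. The groups then compared are no longer the groups that were randomised, and what separates them from the randomised groups depends on the event under study.

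**Working it through.** **Inputs from the article (Participants):** 40% vs 20%, power 80%, significance level 0.05 (sidedness not stated), 10% dropout over the first week, 83 per group.

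**Assumption:** f, the share of pneumonia cases excluded under the rule. The article gives no figure, so a range is shown.

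**1. The plan's own figure.** One-sided 0.05 with continuity correction gives 74 per group, and 74/0.9 = 82.2, rounded up to 83. This matches. The usual two-sided pooled formula gives 82 before dropout and 92 after it. Sidedness is a separate matter. Two-sided 0.05 is used below.

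**2. Baseline without exclusion.** Evaluable per arm: 83 × 0.9 = 74.7, taken as 75. With difference d, power = Φ[(d − 1.96·SE0)/SE1], where SE0 uses the pooled rate and SE1 the separate rates.
- SE0 = √(0.30 × 0.70 × 2/75) = 0.0748
- SE1 = √((0.24 + 0.16)/75) = 0.0730
- Power = Φ[(0.20 − 0.1467)/0.0730] = Φ(0.730) = 76.7%

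**3. Same f in both arms.** The observed risk becomes p(1 − f)/(1 − pf) and the arm size becomes 75(1 − pf). For f = 50%:
- Comparison group: 0.40 × 0.5/(1 − 0.20) = 25.0%, n = 60
- Interventional group: 0.20 × 0.5/(1 − 0.10) = 11.1%, n = 67.5

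| f | Observed risks | Difference (points) | Risk ratio | Odds ratio | Power |
|---|---|---|---|---|---|
| 0 | 40.0% vs 20.0% | 20.0 | 2.00 | 2.67 | 76.7% |
| 10% | 37.5% vs 18.4% | 19.1 | 2.04 | 2.67 | 73.5% |
| 25% | 33.3% vs 15.8% | 17.5 | 2.11 | 2.67 | 67.5% |
| 50% | 25.0% vs 11.1% | 13.9 | 2.25 | 2.67 | 53.7% |
| 75% | 14.3% vs 5.9% | 8.4 | 2.43 | 2.67 | 33.6% |

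**4. Against the dropout allowance.** Expected cases among all randomised: 83 × 0.40 + 83 × 0.20 = 33.2 + 16.6 = 49.8. The 10% allowance covers 166 × 0.10 = 16.6 patients. Excluding one third of the cases (49.8/3 = 16.6) would use all of it.

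**5. Different f in the two arms, no true effect.** Let both true risks be 40%, with 25% of comparison-group cases and 50% of interventional-group cases excluded, starting from 83 per arm.
- Comparison group: 0.40 × 0.75/0.90 = 33.3%, n = 74.7
- Interventional group: 0.40 × 0.50/0.80 = 25.0%, n = 66.4
- The two-sided 0.05 test rejects about 19% of the time. Swapping the two shares gives the same rate of false rejection in the other direction.

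**The case against.** **Timing.** Entry requires no systemic antibiotics and the primary window closes 1 week after baseline. A course longer than 1 week can be recognised only once that window has closed, when the primary event can already be on record. The exclusion sentence also follows directly on the one about withdrawal, so it may mean only that further participation ends. This stands as a limit on certainty: the article does not say that recorded events are discarded. It does not say that they are kept either, and being excluded from the study under a per-protocol analysis points towards loss.

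**LOCF.** If carrying forward covers excluded participants, a recorded pneumonia would persist to the later visits. But LOCF is stated only for the regressions, and the article does not say that excluded participants enter them.

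**Scope.** A reader might infer that the rule removes the primary-outcome cases as a whole. The article does not support that. The rule reaches only some cases, and their share is unknown. Nor does the article show that the cases removed would be the most severe, since it does not link antibiotic duration to severity.

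**Direction.** A reader might infer that a real benefit is necessarily shrunk. With equal f that is true of the risk difference and of power, but the odds ratio is unchanged and the risk ratio rises. With unequal f the bias can favour either arm. Participants know their allocation, so equal f cannot be taken for granted.

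**Size.** Two-sided power is already 76.7% without any exclusion, so f = 25% costs about 9 points (76.7 − 67.5 = 9.2), not the 12.5 suggested by comparison with the planned 80%. The table also takes the exclusions on top of the full 10% dropout, which the article neither confirms nor denies.

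**Purpose.** Protecting the microbiome data from antibiotic effects is a reasonable aim. It could justify setting samples aside, but not taking participants out of the pneumonia comparison.

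**Conclusion.** The point holds in limited form. As written, the exclusion and the per-protocol analysis can together remove some pneumonia cases from the pneumonia outcomes, on a criterion that is a likely consequence of the outcome. The wording is ambiguous, and both readings affect at least one pneumonia outcome.

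Neither size nor direction can be fixed from the document. The losses of risk difference and power rest on the assumed f, the plan's own 40% and 20%, 75 evaluable per arm, a two-sided test and equal exclusion. The false-rejection rate of about 19% rests on one illustrative unequal pattern. Because the validity of the primary comparison is at stake and the correction is nearly free, it should be made before analysis.

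**What to change.** Reconcile Interventions, Outcomes and Data management:

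- Define the pneumonia analyses, primary and secondary, on all randomised participants as allocated, counting every recorded pneumonia whatever antibiotics follow.
- State that the antibiotic rule in Interventions does not remove participants or recorded events from these analyses, and say which of its two meanings is intended.
- Record antibiotic start and stop dates.
- Confine the handling of antibiotic exposure to a microbiome sensitivity analysis that sets aside samples taken after antibiotic start, not participants.

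Deleting the exclusion sentence alone would not be enough, because the per-protocol statement would remain. The cost is a few sentences, two dates per antibiotic course and one sensitivity analysis. No extra patients are needed, and no treatment or treatment-stopping rule changes.
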